### Endpoints

***Primary endpoint***. The primary endpoint is the time to viral clearance from throat/nose swab. Viral presence will be determined using RT-PCR to detect SARS-CoV-2 RNA. Throat/nose swabs for viral RNA will be taken daily while in hospital until there have at least two consecutive negative results. Virus will be defined as cleared when the patient has had ≥2 consecutive negative PCR tests. The time to viral clearance will be defined as the time following randomization until the midpoint between the last positive and the first of the negative throat/nose swabs.

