Biological specimens and laboratory evaluations: On study entry all participants will have a review of clinical investigations done so far. Where an investigation has been performed within the last 24 hours, the results will be recorded, and they will only be repeated if clinically indicated. Study entry laboratory tests will be performed as per the study schedule below.

***Subsequent assessments***. Participants will have daily assessment as per standard of care while in-patient by the hospital staff. While in-patient the study will collect the following data: peripheral oxygen saturation (pulse oximeter), respiratory rate, and FiO2. The use of a ventilator or other non-invasive ventilation device will be recorded each day. Participants will have clinical assessment recorded as per the trial assessment schedule (see
Table 3). The decision to discharge patients will be at the discretion of the attending physician and will depend upon the clinical status of the patient. According to current standard of care, recovery and hospital discharge is dependent upon the patient having had at least two daily consecutive negative PCR throat/nose swabs. Following discharge, participants will be seen on days 28, 42 and 56 post-randomization.

**Table 3. T3:** Trial assessment schedule.

Procedures	Screening	Enrollment/Baseline (Visit 1)	Follow-Up (Visit 2)	Follow-Up (Visit 3)	Follow-Up (Visit 4)	Follow-Up (Visit 5)	Follow-Up (Visit 6)	Follow-Up (Visit 7)	Daily visits to discharge	Day 28 visit	Day 42 visit	Final Study Visit (Day 56)
Informed consent	x											
Demographics	x											
Medical history	x											
Randomization	x											
Physical exam	x	x	x	x	x	x	x	x	x	x	x	x
Throat/nose swab for viral PCR		x	x	x	x	x	x	x	x			
Vital signs	x	x	x	x	x	x	x	x	x			
Weight		x										
CBC w/diff, plts		x		x		x		x				
Serum chemistry ^a^	x			x		x		x				
Blood store (3-5 mls)		x						x				x
ECG (as indicated) ^b*^		x										
CXR	x								x (discharge)			x
Adverse event evaluation			x	x	x	x	x	x	x	x	x	x
WHO ordinal outcome scale **									x (discharge)	x	x	x
EQ5D questionnaire **										x		x
Estimated total blood volumes ml per day ms	6–10	10–12		10–12		10–12		10–12				3–5
Total blood volume over course of study mls (both clinical and research purposes)												52–63

^a^ Urea, Creatinine, ALT, bilirubin

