If a participant chooses to discontinue their trial treatment (chloroquine), they should always be followed up (providing they are willing) and they should be encouraged not to leave the whole trial. If they do not wish to remain in trial follow-up, however, their decision must be respected and the participant will be withdrawn from the trial. The reason for the participant withdrawing should be ascertained wherever possible. Prior to withdrawing from the trial, the participant will be asked to have assessments performed as appropriate for the final visit although they would be at liberty to refuse any or all components of the assessment.

If a participant withdraws from the trial, the medical data collected during their previous consented participation in the trial will be kept and used in analysis. Consent for future use of stored samples already collected can be refused when leaving the trial early (but this should be discouraged and should follow a discussion). If consent for future use of stored samples already collected is refused, then all such samples will be destroyed following the policies of the institution where the samples reside at the time (local or central storage). Participants may change their minds about stopping trial follow-up at any time and re-consent to participation in the trial. Participants who stop trial follow-up early will not be replaced, as the total sample size includes adjustment for losses to follow-up.

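### Participants who leave the trial before viral clearance have no stated route for later routine PCR results, and investigator-led discontinuation can make that censoring depend on arm

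*Protocol article*

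**What the plan says.** **Exit assessment.** Under Discontinuation of treatment and participation: "Prior to withdrawing from the trial, the participant will be asked to have assessments performed as appropriate for the final visit". The participant may refuse any part of it. In Table 3 the only visit labelled final is Day 56. It carries physical examination, blood store, chest X-ray, adverse event evaluation, WHO scale and EQ5D. The row "Throat/nose swab for viral PCR" is marked at Visits 1 to 7 and at the daily visits to discharge, and is blank at Days 28, 42 and 56. Vital signs, blood count and serum chemistry are also blank at Day 56.

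**Data after exit.** For a participant who withdraws, "the medical data collected during their previous consented participation in the trial will be kept and used in analysis". Nothing is said about results obtained afterwards. The footnotes to Table 3 allow clinical-care investigations to be recorded in the CRF, as an option and without reference to people who have left.

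**Routine swabbing.** Subsequent assessments states that, under current standard of care, "recovery and hospital discharge is dependent upon the patient having had at least two daily consecutive negative PCR throat/nose swabs".

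**Who may leave.** A participant who chooses to stop chloroquine is to be followed up if willing. Separately, the investigator may discontinue a participant from the trial for reasons that include non-compliance with the treatment regimen, and an adverse event or disease progression that requires the trial medication to be stopped.

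**Analysis.** The main population is all randomized participants with COVID-19, analysed by randomized arm. The primary endpoint is analysed by log-rank test and Cox model.

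**The concern.** The exit list suits someone who cleared the virus weeks ago. Applied to an in-patient leaving in the first week, it asks for an X-ray and a quality-of-life questionnaire but not for the test that defines the primary endpoint. More important, such a person would normally stay in hospital and be tested again, yet the plan has no route for those results to reach the analysis.

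The investigator-led route is the sharper problem. The control arm receives no trial drug, so a control cannot be discontinued for not complying with chloroquine, or because an adverse event or progression requires chloroquine to be stopped. A chloroquine participant can be, without having withdrawn consent. The instruction to keep following people up is worded for participants who choose to stop treatment, not for those the investigator removes.

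The log-rank test and Cox model require censoring to be unrelated to the outcome within arm. If chloroquine participants who are doing badly, and who may clear late, are removed while still positive, those left at risk would look faster than the arm as a whole. The drug-stopping reasons have no counterpart among controls. Ending follow-up at discontinuation would also affect survival to Day 56.

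**Working it through.** **1. The passages side by side.**

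| Question | What the protocol gives |
|---|---|
| Swabs while in the trial | "Throat/nose swabs for viral RNA will be taken daily while in hospital until there have at least two consecutive negative results" (Endpoints) |
| Event definition | "Virus will be defined as cleared when the patient has had ≥2 consecutive negative PCR tests" (Endpoints) |
| Swab marks in Table 3 | 8 from Visit 1 to the daily visits; 0 at Days 28, 42 and 56 |
| Exit assessment | That of the final visit, i.e. Day 56 |
| Results after exit | No provision |
| Investigator-led discontinuation | From the trial, including for reasons tied to the trial drug |

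An uncleared leaver is therefore censored at about the last trial swab.

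**2. The plan's own power figure.** Inputs from Sample size calculation: log-scale mean 2.17, SD 0.74, N = 240, factor 0.76. Allocation is 1:1, so n = 120 per arm. The significance level is not stated; two-sided 5% is assumed.

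Power = Φ( |ln 0.76| / (0.74·√(2/n)) − 1.96 ) = Φ(0.2744/0.0955 − 1.96) = Φ(0.91) = 81.9%.

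This agrees with the stated 80%. Exactly 80% needs 115 per arm, 230 in all, so the margin is 10/240, about 4%. The protocol says leavers are not replaced because the sample size allows for losses, but the sample size section shows no loss rate.

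**3. Who would leave without the endpoint.** Share not yet cleared at day d = 1 − Φ((ln d − μ)/0.74), with μ = 2.17 in control and 2.17 + ln 0.76 = 1.896 on chloroquine.

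| Day | Control | Chloroquine (factor 0.76) |
|---|---|---|
| 3 | 93% | 86% |
| 5 | 78% | 65% |
| 7 | 62% | 47% |
| 10 | 43% | 29% |
| 14 | 26% | 16% |
| 28 | 6% | 3% |

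The protocol gives no exit rate. Assume 5–10% of 240 (12–24 people) leave around day 5, split evenly between arms. The average uncleared share is (0.78 + 0.65)/2 ≈ 0.71, so about 0.71 × 12 ≈ 9 to 0.71 × 24 ≈ 17 people leave uncleared.

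**4. Power cost.** If leavers' outcomes were wholly lost, the formula in step 2 gives 80.0% at 5% loss (n = 114 per arm), 77.8% at 10% (n = 108) and 72.9% at 20% (n = 96). That is an upper bound on the loss, because censored time carries information. A log-rank simulation (4,000 runs per rate, log-normal times as above, exit day uniform on days 1 to 10 and unrelated to arm or outcome) gave:

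| Exit rate | Full follow-up | Leavers censored | Difference |
|---|---|---|---|
| 5% | 73.6% | 73.0% | 0.6 points |
| 10% | 74.9% | 72.8% | 2.1 points |
| 20% | 74.3% | 70.4% | 4.0 points |

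The level is below 81.9% because the log-rank test is less efficient than a comparison of log means when times are log-normal. Only the differences matter here.

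**5. Bias.** The simulation makes exit unrelated to arm and outcome, so it does not measure bias. The documents give no rate of discontinuation by arm or reason from which to compute one.

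**The case against.** The strongest case against is that the exit visit matters little and much is already covered.

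- Clearance needs two consecutive negatives, so one exit swab would seldom settle it. Swabs are daily in hospital, so an exit swab adds about a day at most. This stands, and it is why the exit visit is the minor part of the point.
- Participants who stop chloroquine by choice stay in follow-up if willing, re-consent is possible, and the informed consent section allows withdrawal from any single aspect of the trial. This stands too. The group that remains is those who decline further follow-up and those the investigator removes. For the first group, collection without permission would be wrong.
- The consent form is not shown and may already offer permission to use routine records. This stands, so the fix is conditional there.
- Handling of censoring belongs to the analysis plan. It does, but an analysis plan cannot restore results that were never collected or permitted.

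A reader might infer more than the documents support:

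- **That leavers' primary endpoint is lost.** Those already cleared have it, and the others contribute time to their last swab.
- **That only pre-withdrawal data may be used.** The text says such data are kept and used; it does not bar later data. The words 'as appropriate' do not forbid an exit swab either.
- **That someone leaving for an adverse event has no safety data near exit.** Vital signs are scheduled daily to discharge and chemistry at Visits 3, 5 and 7, and the Day 56 set adds examination and adverse event evaluation.
- **That routine results would recover the full clearance time.** The discharge rule implies further swabs, but daily swabbing is stated as the trial's schedule, not as routine care.

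**Conclusion.** The point holds as a low-cost improvement to a rule the protocol fixes. The exit assessment refers to a visit without the primary endpoint's test, and routine PCR results after exit have no stated route into the analysis. The investigator may also end participation for drug-linked reasons that exist in one arm only and need no withdrawal of consent.

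The power cost is small: about 1–2 points at an assumed 5–10% exit rate. The case rests on avoidable censoring that may depend on arm and illness course. Its effect on the estimate is not quantified and could be negligible if few are discontinued before clearance. The conclusion assumes that discontinuation from the trial ends outcome collection, which the text implies but does not state, and that leavers who stay in hospital continue to be swabbed, which is inferred from the discharge rule.

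**What to change.** Amend Discontinuation of treatment and participation as follows. None of this changes when treatment is stopped.

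1. State that outcome collection ends only when consent to it is withdrawn. Participants whom the investigator discontinues stay in follow-up for the primary endpoint and survival.
2. Ask those who withdraw for permission to take routine PCR results, discharge date and vital status to Day 56 from the hospital record, and use these in the intention-to-treat analysis. Add a consent option if the form does not already have one.
3. As a minor point, for anyone leaving before confirmed clearance, refer the exit assessment to the in-patient visit set, including the swab, rather than the Day 56 set.

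The cost is a minor amendment, possibly one line on the consent form, and chart abstraction for a few participants. Routine swabs may be less frequent than trial swabs, which would give a coarser clearance time for these people. Study status reports two participants enrolled, so a change at that stage would cover nearly the whole trial.

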Due to the biohazard of SARS-CoV-2 contaminated documents, special safety provisions must be made for how source documents are collected and stored. In the study sites, the study participants may be treated in an isolation area or a negative pressure room, where paper documents are not allowed to be taken out as presumed contaminates. In such cases, the study will apply other appropriate methods for obtaining valid informed consent as detailed in the Oxford University Clinical Research Unit (OUCRU) informed consent standard operating procedures (SOP). The clinician will document the signing of the consent form in the participant’s medical notes. It may be necessary for a photograph or scanned image of the informed consent signature page to be stored as an “electronic source document” rather than retaining a paper version, which will be destroyed to minimize infection transmission risks. A handheld device (e.g., smartphone) will remain in the high-risk zone for this purpose. This will allow for the information to be transmitted electronically as a PDF for archiving following the OUCRU archiving and destruction of essential documents SOP. The person, who gives consent, will retain a copy of this electronic source document. Where possible a consent form will be re-signed at discharge to ensure a hard copy can be handed to the participant and kept for storage. Copies of the informed consent form in English and Vietnamese are provided as
*Extended data*
^27^.

***Screening and eligibility assessment***. After consent has been obtained from the participant or their relative, clinical information including medical history and examination, and weight will be recorded on the case report form (CRF). Routine tests will also be recorded on the CRF as part of the medical history of the current infection. The screening procedures will take place as soon as possible after the clinicians have identified a potential participant from the study hospitals. Recruitment activities will only occur in an in-patient hospital setting and no activities will be carried out outside of the participating hospitals. The target sample size of 240 participants will be enrolled within an anticipated accrual rate of 6–8 months.

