^b^ Daily ECGs performed if on other medication which can prolong QTc. Additional investigations performed for clinical care can be recorded in the study CRF in order to help understanding of the clinical course. * In HTD and if the patient is in ICU, ECG will be measured continuously every one hour daily for 14 days or until discharge if earlier. ** May be administered by telephone call. Note: if it is impossible for the patient to attend day 28, 42, and 56 visits (e.g. community in lockdown, or hospital closed to non-COVID patients) then follow-up can occur entirely by phone. PCR, polymerase chain reaction; CBC, complete blood count; ECG, electrocardiogram; CXR, chest X-ray; WHO, World Health Organization; ALT, alanine aminotransferase; CRF, case report form; HTD, Hospital for Tropical Diseases; ICU, Intensive Care Unit.

In a subset of participants admitted to HTD we will monitor ECG changes, using real-time monitoring. Participants will have up to one-hour ECG continuous recordings daily. The ECG recording will be downloaded from a standard monitor (GE Careview) and stored electronically. ECG changes (including QT interval) will then be analysed by machine learning.

***Discontinuation of treatment and participation***. Each participant has the right to withdraw from the trial at any time. In addition, the investigator may discontinue a participant from the trial at any time if the investigator considers it necessary for any reason including:
Ineligibility (either arising during the trial or retrospectively having been overlooked at screening)Significant protocol deviationSignificant non-compliance with treatment regimen or trial requirementsAn AE which requires discontinuation of the trial medication or results in inability to continue to comply with trial proceduresDisease progression which requires discontinuation of the trial medication or results in inability to continue to comply with trial procedures
Withdrawal of consentLoss to follow up

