### Statistics

***Sample size calculation***. We assume the viral clearance time from throat/nose swabs to have a log-normal distribution. Using data from 14 patients in Ho Chi Minh City and Singapore, we estimated the mean time to clearance (natural log scale) of 2.17 days and standard deviation 0.74 ([name] [name], personal communication, 13 February 2020 and [name] [name], personal communication, 12 February 2020). 120 patients will give 80% power to detect a reduction in the time to viral clearance by at least a factor 0.68. If the trial completes enrolment and is not stopped early due to safety, efficacy or futility, we will enrol 240 patients. A sample size of 240 patients will give 80% power to detect a reduction in the time to viral clearance by at least a factor 0.76.

***Statistical and analytical plans***. Study analysis will be according to an
*a priori* defined statistical analysis plan, which will be completed before database locking. The primary endpoint is virological and robust and will be performed by technicians unaware of the treatment allocation of the patient. In that sense the study therefore is blinded. The time to viral clearance will be defined as the time from randomization to the midpoint between the last positive and the first of at least two consecutive daily negative viral PCR tests on throat/nose swab. Data will be illustrated with time to event curves and analysed using the log rank test and Cox model.

***Secondary endpoints***.

Survival until 56 days after randomization

Overall survival will be visualized using Kaplan-Meier curves and modelled using the Cox proportional hazards regression model with stratification by disease severity. In addition, survival will be modelled with a multivariable Cox regression model including the following covariates in addition to the treatment group: age, comorbid conditions (hypertension, cardiac disease, diabetes, ACEA inhibitor or angiotensin receptor blocker use).

AEs

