The frequency of serious and grade 3 and 4 ARs as well as the frequency of specific AEs will be summarized (both in terms of the total number of events as well as the number of participants with at least one event). The proportion of participants with at least one such event (overall and for each specific event separately) will be summarized and (informally) compared between the two treatment groups based on Fisher’s exact test if the expected number in one of the cells is at most one and the chi-square test if expected number in each cell is larger than one.

Analysis of other secondary outcomes

1. The duration of hospital stay from the time of randomization.2. The number of ventilator-free days during the first 28 days following randomization.3. The time to (all-cause) death following the first 10, 28, and 56 days since randomization.4. The WHO ordinal outcome scale for COVID-19 at days 28, 42 and 56
^24^.5. Fever clearance time.6. Development of ARDS defined by the Kigali criteria
^25^.7. Oxygenation-free days over the first 28 days.

The analyses of these secondary endpoints will be defined in the statistical analysis plan.

***Statistical hypotheses***. The primary null hypothesis is that the rate of clearance of virus from throat/nose swabs is not different between chloroquine compared with standard of care therapy.

***Analysis datasets***. The primary analysis population for all analysis is the full analysis population containing all randomized participants except for those mistakenly randomized without COVID-19. Participants will be analysed according to their randomized arm (intention-to-treat). In addition, the primary endpoint will be analysed on the per-protocol population, which will exclude the following participants: major protocol violations and those receiving less than one week of administration of chloroquine for reasons other than death.

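### The protocol refuses replacement because the sample size allows for losses, but its calculation shows no allowance, and its discontinuation wording lets stopping chloroquine end follow-up

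*Protocol article*

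**What the plan says.** **Allowance for losses.** The section on discontinuation of treatment and participation (Study procedures) states: "Participants who stop trial follow-up early will not be replaced, as the total sample size includes adjustment for losses to follow-up". No rate is given there.

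**The calculation.** Sample size calculation (Statistics) assumes log-normal clearance times: "we estimated the mean time to clearance (natural log scale) of 2.17 days and standard deviation 0.74". It then says "120 patients will give 80% power to detect a reduction in the time to viral clearance by at least a factor 0.68" and, for the complete trial, "240 patients will give 80% power to detect a reduction in the time to viral clearance by at least a factor 0.76". Screening and eligibility assessment sets the same number as the recruitment goal: "The target sample size of 240 participants will be enrolled".

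**Leaving the trial.** The discontinuation section also says "the investigator may discontinue a participant from the trial at any time if the investigator considers it necessary for any reason including". The listed reasons include marked non-compliance with the treatment regimen, and an adverse event or disease progression that makes stopping the trial medication necessary. The text that follows identifies trial treatment as chloroquine. It asks for continued follow-up when a participant chooses to stop it. It also says that data collected before a withdrawal stay in the analysis.

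**Analysis.** Analysis datasets specifies intention-to-treat by randomised arm. The primary endpoint is analysed with a log-rank test and a Cox model.

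**The concern.** There are two linked problems.

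1. The decision not to replace leavers rests on an adjustment that the sample size section does not show. The number enrolled and the number in the power statement are both 240. If no allowance was made, the stated power assumes that nobody is lost. A reader of the discontinuation section would believe otherwise.

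2. The discontinuation wording does not separate stopping the drug from leaving the trial. Control patients receive standard of care alone, so a reason that depends on stopping trial medication, or on not complying with the treatment regimen, can in practice arise only in the chloroquine arm. Investigators know the arm. If such patients leave before two negative swabs, they are censored in one arm for reasons related to toxicity or prognosis. Survival and safety to day 56 are exposed in the same way.

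**Working it through.** **Inputs.** From Sample size calculation: SD 0.74 on the natural log scale, N = 120 with factor 0.68, N = 240 with factor 0.76, 80% power. From Randomization and treatment allocation: 1:1. Assumed, because not stated: two-sided alpha of 5%. A one-sided 5% test gives about 89% power at both sizes and does not match the stated 80%. Loss rates of 5 to 15% are also an assumption.

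**Step 1: reproduce the plan's figures with no loss.** With δ = −ln(factor) and standard error = 0.74 × √(4/N), the normal approximation gives

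N = 4 × [0.74 × (1.960 + 0.842) / δ]²

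- Factor 0.76: δ = 0.2744, N = 228.3, or 230 with equal whole arms.
- Factor 0.68: δ = 0.3857, N = 115.6, or 116.

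In reverse, the factor detectable with 80% power is exp(−2.802 × 0.74 × √(4/N)). This is 0.765 at N = 240 and 0.685 at N = 120. The non-central t calculation gives 0.764 and 0.683, with power of 81.6% at 0.76 and 80.8% at 0.68. So the published factors fit a calculation that counts every enrolled patient.

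**Step 2: apply a loss (t-test, leavers deleted entirely).**

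| Loss | Evaluable of 240 | Power at 0.76 | Factor at 80% power | Evaluable of 120 | Factor at 80% power |
|---|---|---|---|---|---|
| 0% | 240 | 81.6% | 0.764 | 120 | 0.683 |
| 5% | 228 | 79.6% | 0.759 | 114 | 0.676 |
| 10% | 216 | 77.4% | 0.753 | 108 | 0.669 |
| 15% | 204 | 75.0% | 0.747 | 102 | 0.661 |

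**Step 3: how much loss could the rounding hide?** The factors have two decimals, so the true values must be at least 0.755 and 0.675. The second limit binds. It needs about 113.2 evaluable patients by the t-test (1 − 113.2/120 = 5.6%) or 111.3 by the normal formula (1 − 111.3/120 = 7.3%). An unstated loss of up to roughly 5 to 7% would therefore print the same two figures. A 10% loss would print 0.75 and 0.67.

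**Step 4: the rules on leaving, side by side.**

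| Who ends treatment | What the discontinuation section says about follow-up |
|---|---|
| The participant chooses to stop chloroquine | Follow-up continues if the participant is willing |
| The investigator acts, because of non-compliance with treatment or an adverse event or progression that makes stopping the medication necessary | The participant may be discontinued from the trial; no statement that follow-up continues |

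The safeguard in the first row does not cover the second. Keeping earlier data does not replace swabs or visits that never take place.

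**The case against.** **The arithmetic cannot prove that no adjustment was made.** This stands. A loss of about 5% fits the printed figures as well as no loss does, and a rate may be written in the full protocol. What remains is that the article asserts an allowance and its own calculation shows none.

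**The power effect is small and the t-test overstates it.** This also stands. At 5% loss, power is 79.6%, in effect the stated 80%. Deleting leavers altogether is pessimistic: data before withdrawal are kept, the log-rank and Cox analyses use censored time, swabs are daily, and discharge under current standard of care depends on two consecutive negative swabs. Most ordinary losses would come after clearance.

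**A reader might infer that losses bring the planned log-rank test down to about 69% power.** The figures do not support that attribution. In simulation with log-normal times, 240 patients and factor 0.764, the log-rank test has about 73% power with no loss and about 69% with 10% censored before clearance. Only about 4 points come from loss. The rest comes from sizing on log means and analysing with a log-rank test, which is a different matter.

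**A reader might infer that the removal clause is aimed at chloroquine patients or breaks intention-to-treat.** Neither follows. The clause is permissive, is worded for any participant, and lists reasons common to both arms, such as ineligibility. Censoring a leaver in the randomised arm is compatible with intention-to-treat. What stands is a risk of informative censoring, through the drug-linked reasons.

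**Conclusion.** The point holds in two limited parts.

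- **Sample size.** The claimed adjustment is not shown. The enrolled and powered numbers are identical, and a 10% allowance is incompatible with both printed factors. The cost is about 2.6 points below 80% at 10% loss (80 − 77.4) and 5 points at 15%. These are upper bounds for loss that is balanced between arms and unrelated to outcome. They rest on two-sided 5% and on assumed loss rates.
- **Follow-up.** The wording allows drug-linked removal from the trial that can in practice occur in one arm only, without the follow-up safeguard that applies when the participant chooses to stop. The documents give no rate for such removals, so the size of any bias cannot be stated.

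Both should be corrected. Neither shows that the trial is seriously underpowered.

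**What to change.** 1. Delete the claim in the discontinuation section that the total includes an adjustment for losses, or restate Sample size calculation with the allowance shown: loss rate, evaluable number, alpha and resulting factor. For example: 240 enrolled, 10% loss, 216 evaluable, 80% power for a factor of 0.75.
2. Reconcile the investigator's grounds for discontinuation with the paragraph on participants who choose to stop. State that ending trial medication, for whatever reason and at whoever's decision, does not end the scheduled swabs or the day 28, 42 and 56 follow-up unless consent is withdrawn. This leaves every clinical rule on when the drug is stopped as it is.

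The cost is wording, plus a slightly less favourable detectable factor if the allowance is shown. No patients are added, and no visits beyond those already scheduled.
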